#### Stigma Measurement and Prospective Assessment

To explore how HIV and MSM stigmas compound to influence health seeking and health risk behaviors, the protocol calls for adaptation of validated stigma measures to the context of MSM in South Africa. To adapt stigma measures for MSM in South Africa, we conducted a brief literature review to identify scales that were validated for use in other populations and that fit well into Earnshaw’s Stigma Measurement model [13], which focuses on anticipated, internalized, and experienced stigma. An expert panel was convened to identify preferred scales and scale items (Multimedia Appendix 5) and to recommend appropriate adaptations of items or scale formats. Following this process, we conducted four focus groups, with 21 participants in total, to identify emic experiences with stigma for new item development. Focus groups included a pile-sorting activity to identify whether scale items aligned with Earnshaw’s stigma subdomains of anticipated, internalized, and experienced stigma. This was followed by cognitive interviews to explore participant comprehension of individual scale items (Multimedia Appendix 6). Results from focus group discussions and cognitive interviews were shared with the expert review panel, allowing for consultation on the optimal tailoring and adaptation of items.

The finalized set of stigma scale items is included in the baseline questionnaire for the pilot study that will be completed by an estimated 160 HIV-uninfected respondents and 40 HIV-infected respondents. Assessment of scale validity will include determination of scale reliability and scale factors and also correlational validity based on scale correlations with theoretically supported constructs.

Analysis will assess the impact of the pilot study’s provision of combination HIV prevention services on HIV and MSM stigmas. We hypothesize that for MSM enrolled in Sibanye, access to combination HIV prevention services provided in a culturally competent atmosphere will result in reductions in anticipated, internalized, and enacted MSM and HIV stigma.

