#### Pilot Study

##### Overview

The pilot study will be a prospective one-year assessment of the implementation of a package of combination HIV prevention services. In addition to providing information on acceptability and uptake of the prevention package, the longitudinal study will develop capacity for conducting prospective data collection and providing prevention interventions and services. Data from the pilot study will also allow for refinement of estimates of key model parameters and support development of training curricula.

Approximately 200 MSM, 100 each in Cape Town and Port Elizabeth, will be followed for a period of 12 months. Participants will be offered prevention interventions, including condom choices with an assortment of styles, sizes, and features; condom-compatible lubricant choices, including water- and silicone-based types; couples HIV testing and counseling (CHTC) [14,15]; and PrEP for eligible men. Non-occupational post-exposure prophylaxis (nPEP) for men with an exposure at high risk for HIV transmission will be made available. Data on service utilization, condom use, HIV and STI incidence, acceptability of the prevention package, HIV-related knowledge, and other outcomes will be collected.

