##### Participants and Enrollment

Men eligible to participate in the study will be aged 18 years and older, self-report anal intercourse with a man in the past year, be current residents of the study city, plan to stay in the city for the next year, be able to answer survey questions in English, Xhosa, or Afrikaans, be male sex at birth, be willing to provide contact information, and have a phone to facilitate the scheduling of study clinic visits. All study participants will provide written informed consent prior to participating in the pilot study.

The study will enroll both MSM who are living with HIV (HIV-positive) and those who are HIV-negative. Up to 20% of men followed for one year will be living with HIV. Additional HIV-positive men recruited will be enrolled for a baseline visit only and will not count towards the 100 men per site sample size. Recruitment and enrollment will be monitored in stages to ensure sufficient HIV-negative men are enrolled to adequately assess elements of the HIV prevention package. Enrollment of HIV-positive men will be monitored in steps. Once five HIV-positive men are enrolled prospectively at baseline, prospective enrollment of positives will pause until 20 HIV-negative men are enrolled. Men who seroconvert during follow-up will remain in the study for the full follow-up period. Recruitment activities will be conducted for approximately 3 months or until 100 MSM have been recruited and enrolled in each city. In both Cape Town and Port Elizabeth, MSM will be recruited from multiple areas including urban areas, peri-urban communities, and township areas in order to recruit diverse communities of MSM. We will employ different methods of recruitment, including event- and venue-based, online, participant referral, and walk-ins at study clinics. Men who meet the eligibility criteria during recruitment will be asked to provide contact information and be scheduled for an enrollment baseline visit.

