##### Study Intervention

The intervention package will be available starting at baseline and continuing throughout the study and will include condom and condom-compatible lubricant choices, risk reduction counseling, CHTC, linkage to care for HIV-positive men, and PrEP with emtricitabine/tenofovir disoproxil fumarate for eligible men for initiation at a 1-month or 4-month visit (Figure 4).

At their baseline visit, all participants will receive a package with condom and condom-compatible lubricant choices: ribbed, colored, flavored, fitted, thin, and flared condoms, and silicone-based and water-based lubricants. Participants will be given a Condom Scorecard to rate their condom preferences, to be returned at their next study visit (Multimedia Appendix 7). At all follow-up study visits, participants will be encouraged to pick up their preferred condom and lubricant types. Participants can also drop in to each study clinic during study clinic hours to pick up additional condoms and condom-compatible lubricant.

HIV testing will be provided to all men at their baseline visit. Risk-reduction counseling will be provided to all men regardless of their HIV status and at all standard and PrEP visits. Risk reduction counseling will be client-centered, according to the Centers for Disease Control and Prevention’s (CDC) Fundamentals of HIV Prevention Counseling curriculum. HIV testing will be provided to all men at their 3, 6, and 12-month visit who tested negative at their previous visit. HIV testing will be performed by counselors trained in using South African provincial HIV testing protocols.

Participants will be invited to schedule CHTC appointments with a clinic counselor at any point after they complete their baseline visit. The CHTC model differs from individual testing in that a couple receives HIV testing and counseling at the level of the couple, with tailored messaging based on dyadic characteristics. Participants can attend multiple CHTC sessions with different partners; these partners do not have to be enrolled in the study to participate. All CHTC sessions will be performed by counselors who completed a 3-day training curriculum on CHTC for MSM.

Men who test positive for HIV at baseline or during the study will be linked to HIV treatment and care services as needed, including antiretroviral medication and mental health services. Referrals will be made to local providers known to be MSM-friendly.

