##### Data Collection

Data will be collected via case report forms, self-administered surveys during study visits, and monthly short message service (SMS) surveys. Paper-based case report forms will be used to capture eligibility and enrollment data, as well as all clinical assessments, interventions, laboratory results, adverse events, and social harms reporting (Multimedia Appendix 8). All case report forms will be completed by study staff, rather than participants. These forms will be sent by scan to Emory University, with data captured using DataFax, and securely stored in participant study binders at the DTHF and HSRC offices.

At each standard study visit, participants will complete surveys on iPads or computers via SurveyGizmo, which has secure servers and a Health Insurance Portability and Accountability Act business partner agreement with Emory. Surveys will be offered in English, Xhosa, and Afrikaans (Multimedia Appendix 9). Surveys were translated from English to Xhosa and Afrikaans, then back-translated to ensure conceptual and cultural equivalence. These surveys will collect data on demographics, current use of health care services, history of HIV and STI testing, outness to health care providers, alcohol and substance abuse, history of sexual activities and condom and condom-compatible lubricant use, barriers to safer sex practices, stigma, knowledge of HIV transmission and prevention strategies, and the participant’s sexual network.

An SMS survey will be sent to consenting participants each month. These brief surveys will collect information on recent sexual activity with male and female partners, including the number of partners, frequency of sex acts, condom use, lubricant use, and HIV testing outside of the study.

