##### Data Analysis Plan

The primary design for analysis will be a pre-post design. For measures that are collected from MSM participants (eg, use of condom and condom-compatible lubricant, disclosure of male sex partners to providers), data will be compared between baseline surveys and follow-up surveys. Bivariate analyses will be conducted by comparing proportions of men reporting a behavior between baseline and follow-up, using chi-square statistics. If differential retention results in follow-up data being available from a group with substantially different characteristics (eg, if older men are differentially retained, so that the 12-month participants are considerably older than the baseline sample), stratified analyses or regression modeling may be used to account for potential confounders. For biological measures, we will describe the prevalence of HIV, syphilis, chlamydia, and gonorrhea at baseline and will calculate the incidence of HIV, syphilis, chlamydia, and gonorrhea during prospective follow-up. We will conduct an intent-to-treat analysis; participants who are lost or withdraw from the study will be considered failures in analysis of uptake of the particular intervention or service of interest. HIV-positive participants who are enrolled for a baseline visit only will be included in analyses to understand prevalent behaviors and clinical features, like HIV viral load, access to care, and condom use.

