##### Sample Size

Our pilot feasibility study is not powered to measure differences in pre-post measures in clinical outcomes; rather, we hope to develop reasonable estimates of the prevalence of certain behaviors at baseline and of the incidence of HIV infection and STIs, which may be important endpoints in a larger, future prevention trial. The choice of 100 participants per site is based on feasibility within time and budgetary constraints and will provide reasonable estimates of key parameters, including retention in the cohort and uptake of PrEP.

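### The uptake analysis counts every lost or withdrawn man as a failure, with no exception for uptake recorded before he was lost, so reported uptake is biased downward and mixed with retention

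*Protocol article*

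**What the plan says.** The Data Analysis Plan announces an intent-to-treat analysis and explains it in one clause: "participants who are lost or withdraw from the study will be considered failures in analysis of uptake" of the service in question. The clause does not separate a man lost before he took up a service from a man lost afterwards.

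Three other parts of the pilot description bear on this:

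- **Timing.** Under Study Intervention, eligible men can begin PrEP at a visit at month 1 or, failing that, at month 4. CHTC can be booked at any point once the baseline visit is complete. Under the pilot's Overview, "Approximately 200 MSM, 100 each in Cape Town and Port Elizabeth, will be followed for a period of 12 months".
- **Recording.** Under Data Collection, staff-completed case report forms capture eligibility and enrolment data together with "all clinical assessments, interventions, laboratory results, adverse events, and social harms reporting".
- **Purpose.** The Sample Size section says that 100 men per site will give reasonable estimates of key parameters, "including retention in the cohort and uptake of PrEP".

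**The concern.** Scoring a missing outcome as a failure is a convention for outcomes that are unknown. A PrEP start or a CHTC session that staff have entered on a form is known, and the man's later disappearance does not undo it. If he is then scored as a failure, an observed success is overwritten.

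Two things follow. First, the uptake estimate can only move down, because the rule never turns a non-user into a user. Second, the reported figure no longer measures willingness to start. It measures starting and then staying in the cohort until the end. The Sample Size section lists retention and PrEP uptake as distinct quantities, and the article intends the pilot's results to refine the model parameters and inform the design of a larger trial. A reader who sees low uptake could not tell whether men declined the service or accepted it and later left the study.

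**Working it through.** **The plan's own figure.** There is none to reproduce. The article gives no expected uptake, expected retention, significance level or power, and 100 per site is a feasibility choice.

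**Inputs from the article**

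- Cohort: 200 men, followed for 12 months (pilot Overview).
- HIV-negative men: the article says "Up to 20% of men followed for one year will be living with HIV", so at least 200 × 0.80 = 160 are HIV-negative at the cap. The stigma section agrees: "an estimated 160 HIV-uninfected respondents and 40 HIV-infected respondents". I take 160 as the PrEP denominator; the other PrEP eligibility criteria can only reduce it.
- Time in which a starter can be lost: 12 − 1 = 11 months after a month 1 start, and 12 − 4 = 8 months after a month 4 start.

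**Inputs assumed**

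- U, the true proportion who ever start: 30%, 50% or 60%.
- L, the share of starters later lost or withdrawn: 5% to 30%.

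**Effect of the rule.** Reported uptake = U × (1 − L); bias = −U × L; starters recoded as failures = 160 × U × L.

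| U | L | Reported uptake | Bias (points) | Starters recoded, of 160 men |
|---|---|---|---|---|
| 30% | 5% | 28.5% | −1.5 | 2.4 |
| 30% | 10% | 27% | −3 | 4.8 |
| 30% | 20% | 24% | −6 | 9.6 |
| 50% | 10% | 45% | −5 | 8 |
| 50% | 20% | 40% | −10 | 16 |
| 50% | 30% | 35% | −15 | 24 |
| 60% | 30% | 42% | −18 | 28.8 |

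**Comparison with sampling error.** The 95% half-width is 1.96 × √(p(1 − p)/n). At p = 50% this is 7.7 points for n = 160 and 11.0 points for one site with n = 80. At U = 50% the bias exceeds 7.7 points once L is above 7.7/50, about 15%. At L = 10% it is 5 points, inside the half-width. At U = 30% the half-width for n = 160 is 7.1 points, and the biases of 1.5 to 6 points in the table are all inside it.

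**Mixing with retention.** A reported 40% fits true uptake of 0.40/0.95 = 42.1%, 0.40/0.90 = 44.4%, 0.40/0.80 = 50.0% or 0.40/0.70 = 57.1%, depending on whether 95%, 90%, 80% or 70% of starters stay. The reported figure alone cannot tell these apart.

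**After the change.** If recorded uptake is kept, U = 50% and L = 20% give 80/160 = 50% instead of 64/160 = 40%. Men lost before any uptake still count as non-uptake, so keeping all eligible men in the denominator is not the fault.

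**The case against.** The strongest reply is that the clause can be read more kindly. Keeping every man in the denominator and scoring only unknown outcomes as failures is common practice, and the authors may have meant no more than that. They may also have meant continued use at 12 months, for which scoring lost men as failures is reasonable. The outcomes are set out in Figure 5, which is not shown, and the article condenses a fuller protocol. This stands as a limit on how the rule will be applied. It does not remove the point, because the clause says uptake and states neither restriction.

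Four stronger readings are tempting, and the documents do not support them:

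- **Condom uptake is merely retention.** A reader might infer this because "At their baseline visit, all participants will receive a package with condom and condom-compatible lubricant choices". But no section defines condom uptake as receipt of that package. Later pick-up is a different measure, and condom and lubricant use is analysed separately through surveys.
- **Loss will be counted twice in the model or the future trial.** Nothing says that reported uptake will be multiplied by retention.
- **Uptake and retention are what the pilot exists to estimate.** The Sample Size section gives them as examples of key parameters, after naming baseline behaviours and the incidence of HIV and STIs.
- **The intent-to-treat label must go.** It is loose in a study without randomised arms, but the text says at once what it means, and removing it changes no result.

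**Conclusion.** The point holds as a fault in a stated scoring rule. Followed literally, the rule recodes documented PrEP starts and CHTC sessions as failures, lowers reported uptake by U × L, and mixes uptake with retention. The direction is certain under the literal reading. The size is not, because it rests wholly on assumed values: from 1.5 points (U = 30%, L = 5%) to 18 points (U = 60%, L = 30%), and 10 points at U = 50% and L = 20%.

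A reader might conclude that the pilot cannot proceed until this is changed. The documents do not support that. This is a feasibility pilot, the Sample Size section says it is not powered for pre-post differences in clinical outcomes, and ever-uptake stays recoverable from the case report forms. It is a worthwhile and nearly free correction to an estimate that the article itself calls key.

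**What to change.** Amend the clause in the Data Analysis Plan along these lines:

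- Keep all eligible men in the denominator for each service.
- Score uptake as ever documented in clinic records. A man with documented uptake counts as uptake whatever happens to him later.
- Count as non-uptake only men with no documented uptake, including those lost before any.
- Report persistence separately, with lost men scored as not persistent, and report retention as its own figure.

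If Figure 5 defines uptake as continued use at a later visit, state that definition in the Data Analysis Plan and report ever-uptake beside it.

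The cost is about two sentences of analysis wording. No extra data, visits or participants are needed, since the case report forms already hold what is required.

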##### Sample Size

Our pilot feasibility study is not powered to measure differences in pre-post measures in clinical outcomes; rather, we hope to develop reasonable estimates of the prevalence of certain behaviors at baseline and of the incidence of HIV infection and STIs, which may be important endpoints in a larger, future prevention trial. The choice of 100 participants per site is based on feasibility within time and budgetary constraints and will provide reasonable estimates of key parameters, including retention in the cohort and uptake of PrEP.

## Results

### Phase I: Literature Review

In total, 3800 documents were collected from 67 countries. Information gathered from the literature review has been made available on the Internet as a searchable electronic library. Ultimately, 2600 unique records were entered into a database, which can be viewed on the mp3docs website [17].

### Phase II: Modeling

The results of the modeling activities were presented at a plenary session at the 2013 Conference on Retroviruses and Opportunistic Infections [18], and in a published manuscript [7]. The modeling results indicate that regular HIV testing and promotion of condom use produce significant and important benefits in preventing new HIV infections among South African MSM, even in the context of high coverage of early treatment of HIV-positive men and high coverage of PrEP for at-risk HIV-negative men. With a combination package that achieves a 15% reduction in unprotected anal intercourse, some PrEP coverage, some increase in ART treatment services, and some increase in HIV testing, approximately a 35% reduction in infections can be achieved over 5 years. Modeling also found that the combined effects of the four model components to the package were not simply additive; there are some interaction effects. For example, there is an interaction between the HIV testing component and the PrEP component. If testing is increased, then PrEP as an intervention becomes more powerful because more persons become eligible for PrEP. In addition to estimating the impact of these interventions on the epidemic among South African MSM, these findings suggest that the demonstration of acceptability of a packaged prevention approach is a critical next step in optimizing prevention services for MSM in Africa.

A by-product of our modeling and simulation work was an evaluation of the sources of variation in the spread of HIV that arise from overlapping sexual networks and heterogeneity in biological and behavioral risk factors. These sources of variation are not routinely accounted for in the design of HIV prevention trials. Our work on agent-based modeling in the Sibanye MP3 project has led to useful methods for calculating required sample sizes in the design of HIV prevention trials [7].

### Phase III

#### Formative Qualitative Assessment

A qualitative assessment involving in-depth interviews and focus groups with MSM and HIV service providers was conducted in 2012 to obtain information regarding the acceptability and optimal methods of providing HIV prevention interventions for MSM.

Findings from the qualitative data collection were used to inform the components of the prevention package. Data collection for the formative assessment, including 79 in-depth interviews and surveys, six focus group discussions with health care providers and four with MSM, was completed in early 2012. Analysis of qualitative data has informed development of the pilot study interventions. For instance, in focus group discussions participants identified access to condom-compatible lubricant as a high priority service. During in-depth interviews, a number of men discussed using petroleum-based lubricant, and these men often experienced condom breakage. In part based on these findings, we decided to include in the intervention silicone-based lubricant in addition to water-based lubricant to enhance lubricant choice and fulfill the demand for lubricant provision. The analysis of qualitative data to date has also led to a manuscript regarding the contexts of condom use [8] and a manuscript regarding repeat HIV testing [19].

#### Provider Training

A total of 37 providers attended the 2-day training in Port Elizabeth, including physicians, nurses, and clinical officers from across the Eastern Cape. Participants prepared for the training by reading distributed materials in advance of participation. While the goal of the training was to increase provider skills for Sibanye, a secondary benefit was the increased clinical and cultural competence of these providers in addressing the health-related needs of MSM. Among participants who were trained and completed evaluations, many of the attendees (76%, 28/37) reported that they lacked knowledge to care for MSM prior to the training. The training was well received with 100% endorsing a statement that it is important to be sensitized to MSM needs and to learn about MSM and 100% indicating they would recommend this training to colleagues.

